### Recruitment

Approximately 200 families with overweight or obese children aged between 5–9 years old are being recruited, three cohorts during 2005 and one cohort during 2006 from the Hunter (population approximately 550 000) and Illawarra regions (population approximately 380 000) of New South Wales, Australia. Recruitment for each cohort commences approximately eight weeks prior to each baseline assessment. Numerous recruitment strategies are employed to enhance recruitment success and include: personalised letters sent to school principals and counsellors inviting them to promote the study within their school and in school newsletters; articles and posters placed in general practitioner (GP) surgeries, shopping centres and public libraries, 'GP Newsletters' and other GP communication networks and in pediatric dietetic departments at local hospitals; and delivery of presentations to both school principals and at pediatrician meetings. The university media units at each site distribute media releases resulting in newspaper articles and radio and television interviews and finally paid advertisements are placed in local newspapers. Interested parents are encouraged to contact the study sites directly via the study phone line. Eligibility is determined using a standardised telephone screening script, which addresses specific inclusion/exclusion criteria (Table 1). Eligible families are then sent an information sheet, detailing each intervention, their anticipated benefits, their required commitment level, the researchers involved in conducting the study and a consent form. Once written consent is obtained the participants are randomized (see Randomization section) to one of the three study arms. Participants are notified of their allocated trial group initially by telephone with confirmation by mail. Finally, recruited participants are sent a medical screen, to be completed by their GP and to be returned at the baseline assessment. Only one child from each family is able to be recruited.

**Table 1 T1:** Inclusion and exclusion criteria for recruitment into HIKCUPS.

**Inclusion Criteria**	**Exclusion Criteria**
• Overweight/obese^1^	• Extreme obesity (BMI *Z*-score >4)
• 5.5–9 years of age	• Known syndromal cause of obesity
• Pre-pubertal (no pubic hair)	• Long term steroid use
• Generally healthy	• Medications associated with weight gain
	• Chronic illness
	• Significant dietary restrictions

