### Timelines for programs

The baseline, 6-, 12- and 24-month assessments and the face-to-face group sessions are delivered on the university campus at both sites. The baseline assessments, which occur approximately two weeks before the face-to-face sessions commence are conducted over two sessions. Assessments undertaken at the first session include: anthropometry; the sit-to-stand transfer; blood pressure; fasting blood collection and instruction on how to correctly wear the accelerometer. Session One is conducted early in the morning and children are offered an anaesthetic patch to minimise discomfort during blood collection and are provided with breakfast following the blood collection. Both the children and their parent's attend Session Two. The children complete the quality of life and perceived competence questionnaires and have their fundamental movement skills videoed. Parents complete four questionnaires: the Food Frequency Questionnaire; the Child Feeding Questionnaire; the sedentary behaviour and physical activity questionnaire (CLASS) and the quality of life questionnaire (PedsQL™).

Assessments identical to those conducted at baseline are repeated at 6-, 12- and 24-months following the start of the face-to-face sessions. To maximise adherence to these sessions, participants are sent newsletters (two months before the follow-up assessments) and a parent/self-written postcard as a reminder of their program goals, and each child is also sent a birthday card. A HIKCUPS t-shirt is also given to each child at the start of the program to facilitate a sense of community with other children. Parking vouchers or permits are supplied to participants for all assessments and programs. The timeline for each cohort is shown in Figure 2.

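### Families are randomised and told their arm before the GP medical screen and the baseline assessment, so pre-baseline losses, late eligibility failures and family-reported or accelerometer baselines can depend on allocation

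*Protocol article*

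**What the plan says.** The Recruitment section sets out the order of events.

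- Screening is by telephone: "Eligibility is determined using a standardised telephone screening script, which addresses specific inclusion/exclusion criteria (Table 1").
- Families found eligible receive an information sheet and a consent form.
- Allocation follows consent: "Once written consent is obtained the participants are randomized (see Randomization section) to one of the three study arms".
- The result is disclosed: "Participants are notified of their allocated trial group initially by telephone with confirmation by mail".
- The clinical check comes last: "Finally, recruited participants are sent a medical screen, to be completed by their GP and to be returned at the baseline assessment".

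Timelines for programs gives the date of the baseline: "The baseline assessments, which occur approximately two weeks before the face-to-face sessions commence are conducted over two sessions". Session One holds anthropometry, the sit-to-stand test, blood pressure, fasting blood and accelerometer instruction. Session Two holds the child and parent questionnaires and the movement-skill video.

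Two safeguards are stated. Under Assessor blinding, data collectors do not know the arm, and families are asked not to disclose it. Under Statistical analyses, the analysis is by intention to treat, using either multi-level modelling or repeated-measures ANOVA and ANCOVA with the pre-test as adjuster.

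**The concern.** Randomisation protects a comparison from the moment of allocation. What happens between allocation and the first measurement is open to influence by the arm if the family knows it. Here that interval contains three things that should not depend on the arm.

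1. **Whether the family stays.** The arms ask for different commitments: parents attend the diet program, children attend the activity program, and both attend in the combined arm. Families have already read about the benefits and demands of each, so they may hold preferences.
2. **Whether the child proves eligible.** No measured BMI or clinical examination is described before allocation.
3. **What is recorded as baseline.** Diet, feeding practices, sedentary time, quality of life and perceived competence are reported by families who know their arm. The accelerometer is worn by children who may know whether they are about to start an activity program.

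At stake are the comparability of the arms at the point where data begin, and the pre-test values later used to adjust the outcomes.

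**Working it through.** The point rests on the order of events and not on a figure in the plan, so the check is to set the sections side by side.

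**Step 1: order of events.** From Recruitment and Timelines for programs: telephone screen, consent, randomisation, notification, GP form sent out, baseline (GP form returned, Sessions One and Two), group sessions. No other section places the GP form or any measurement before allocation. Figures 1 and 2 are not available to check.

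**Step 2: length of the exposed interval.** "Recruitment for each cohort commences approximately eight weeks prior to each baseline assessment". The gap between learning the arm and baseline is therefore bounded by roughly eight weeks, and is shorter for families recruited late.

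**Step 3: which eligibility criteria await baseline.** Table 1 lists a BMI cut-point, a BMI z-score ceiling, pre-pubertal status, general health, and several exclusions for illness, medication and diet. A parent can report most of the exclusions by telephone. Study-measured height and weight first appear at Session One, and the GP's information arrives the same day. BMI, and perhaps pubertal status, are the criteria most clearly left unverified at allocation.

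**Step 4: exposure by type of measure.**

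| Measure | Source at baseline | Exposure to known allocation |
|---|---|---|
| Food frequency, child feeding, activity and sedentary-behaviour (CLASS) questionnaires | Parent | Reporting and selective loss |
| Quality of life | Parent and child | Reporting and selective loss |
| Perceived competence | Child | Reporting and selective loss |
| Accelerometry | Device worn by the child | Changed behaviour or wear, and selective loss |
| BMI z-score, waist (primary) | Blinded assessor | Mainly selective loss |

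**Step 5: do the stated safeguards close the gap?** Assessor blinding does not blind the family. Intention to treat keeps a child in the arm assigned, but ANCOVA needs a pre-test. A multi-level model could use a child who missed baseline and attended follow-up. Neither can use a family that left before baseline and never returned.

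**Step 6: is there time to reorder?** Baseline is about 14 days before the group sessions, and accelerometers are worn for eight consecutive days. If wear starts at Session One, 14 − 8 = 6 days remain after wear ends. If randomisation follows Session Two without waiting for the wear to finish, the notice is longer but still under two weeks. The stratification factors, gender and site, are known before baseline, so they do not stand in the way.

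**The case against.** The strongest reply is that the risk is real in kind but contained.

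- **Eligibility is settled before consent, by telephone.** A reader might infer from the order that children are removed after allocation on the GP form or on measured BMI. The article does not say so. It neither states the purpose of the GP form nor describes any exclusion at baseline. What stands is narrower: if such failures are acted on, they are acted on after the arm is known.
- **The primary outcomes are objective and measured blind.** This stands, and it limits the concern for BMI z-score and waist mainly to who turns up.
- **All three arms are active, and families consent knowing what each involves.** This makes differential withdrawal less likely than with an untreated control, but does not exclude it. The Randomization section itself argues that an unacceptable allocation could harm retention, although it says so of a no-intervention arm.
- **Intention to treat is promised, and Figure 1 may already show losses by arm.** Both are fair. A reader might infer that children without a baseline are dropped unannounced. No section says that, and the detailed handling may lie in a fuller document.
- **The food frequency questionnaire looks back six months.** This dilutes a true change in diet after notification, but not a change in how diet is reported.

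One might also want to put a number on the bias by multiplying an assumed excess loss by an assumed difference between lost and retained children. The article supplies neither figure. The calculation would also describe an unadjusted mean, whereas the plan adjusts for pre-test. Only a difference in outcome given baseline would then matter for children lost.

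**Conclusion.** The concern holds as a stated feature of the design. Allocation is made and disclosed before the GP screen and before baseline, and nothing else in the article undoes that. The consequence is most direct for family-reported secondary outcomes and for accelerometry, where the baseline itself may be shifted and then used as the adjuster. For BMI z-score and waist the remaining route is mainly selective loss between notification and baseline.

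The size cannot be derived, because no count of pre-baseline losses or eligibility failures is given for any arm. The article does not show that such losses occurred, that they differed by arm, or that the primary comparison is biased. The conclusion assumes that the order in Recruitment is the order followed in practice and that the figures not shown do not contradict it.

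**What to change.** **Cohorts not yet allocated.** Move two steps. Obtain the GP form and complete baseline Sessions One and Two, preferably with the eight days of accelerometer wear, and only then randomise and notify. The GP form is already due back at baseline, so its own timing need not change. Blinding at the baseline assessment then follows automatically.

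**Cost.** No new type of visit is needed, but there are three drawbacks. Families get about six days' notice of their group if the wear is completed first, and somewhat more but under two weeks if it is not. That is tight for contact by telephone and mail. Some baseline visits will be spent on children who turn out to be ineligible. Baseline conditions will differ between earlier and later cohorts, which should be stated when cohorts are pooled.

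**Cohorts already allocated.** Keep all randomised children in the intention-to-treat set. Report withdrawals before baseline and eligibility failures by arm. State that baselines in these cohorts were collected after allocation was known, naming the family-reported and accelerometer measures as the ones most exposed. This costs only reporting effort.

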### Randomization

To randomly allocate participants to one of the three intervention groups the bias coin method of allocation, using a computer-based random number-producing algorithm, is used. This method ensures an equal chance of allocation to each group. Stratification by gender and site is done to ensure an equal representation in groups at each site. Only one study member at each site has access to the allocation codes and these are stored on a password-protected computer.

The study has no control group in the conventional sense of 'no treatment', 'waiting list' or 'typical care'. There were two compelling reasons for this: (i) every child who is overweight is deserving of an intervention and is unlikely to remain at a stable level of overweight [28] providing a strong ethical case against a non-intervention control group; and (ii) extensive recent publicity related to childhood obesity has markedly increased awareness and 'no intervention' is likely to be unacceptable to participants potentially resulting in poor retention and follow-up, thus compromising the study integrity. The flow of all participants following recruitment and randomization is summarized in Figure 1.

**Figure 1 F1:**
[figure not shown]
Flow of participants recruited into the HIKCUPS trial. DM = parent-centered dietary modification program, PASD = child-centered physical activity skill-development program. DM+ PASD = combined parent-centered dietary modification program and child-centered physical activity development program. (* 75 people did not wish to participate or have any further contact).

### Timelines for programs

The baseline, 6-, 12- and 24-month assessments and the face-to-face group sessions are delivered on the university campus at both sites. The baseline assessments, which occur approximately two weeks before the face-to-face sessions commence are conducted over two sessions. Assessments undertaken at the first session include: anthropometry; the sit-to-stand transfer; blood pressure; fasting blood collection and instruction on how to correctly wear the accelerometer. Session One is conducted early in the morning and children are offered an anaesthetic patch to minimise discomfort during blood collection and are provided with breakfast following the blood collection. Both the children and their parent's attend Session Two. The children complete the quality of life and perceived competence questionnaires and have their fundamental movement skills videoed. Parents complete four questionnaires: the Food Frequency Questionnaire; the Child Feeding Questionnaire; the sedentary behaviour and physical activity questionnaire (CLASS) and the quality of life questionnaire (PedsQL™).

Assessments identical to those conducted at baseline are repeated at 6-, 12- and 24-months following the start of the face-to-face sessions. To maximise adherence to these sessions, participants are sent newsletters (two months before the follow-up assessments) and a parent/self-written postcard as a reminder of their program goals, and each child is also sent a birthday card. A HIKCUPS t-shirt is also given to each child at the start of the program to facilitate a sense of community with other children. Parking vouchers or permits are supplied to participants for all assessments and programs. The timeline for each cohort is shown in Figure 2.

**Figure 2 F2:**
[figure not shown]
Time line for the HIKCUPS trial.

### Sample size considerations

Our proposed sample size is based on the assumption that a 50% reduction in weight velocity over a 12-month period would be considered by the investigators as a successful outcome, changes in BMI (primary outcome variable) of 0.26–0.58 SD can be expected among children over a one-year period with the variation dependent upon age, degree of overweight, and height ([name], personal communication). Using the most conservative of these values (0.26 SD), a sample size of 28 participants in each of the interventions, at each site, would detect a difference in mean BMI SD score of 0.26 at baseline using an independent samples *t*-test at *p *< 0.05 with a statistical power of 0.80. Taking into consideration a 20% dropout a total of 216 participants might need to be recruited.

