### Statistical analyses

Analysis will be on an intention-to-treat basis using the 6-month follow-up as the initial endpoint. Prior to analysis normality and equal variance of the data will be assessed using a Kolmogrov-Smiranov test (with Lillefors' correction) and Leven median test, respectively. Main and interaction effects for all primary and secondary outcome variables will then be determined by either multi-level modelling or a repeated measures ANOVA and simple ANCOVA with the pre-test for each group used to adjust the post-test. Co-variates that may be used are: site, sex, and child and parent program participation rates (to control for the possibility that the combined effect of DM + PASD program is not just due to an increased number of sessions with researchers). A MANOVA design will also be used to analyse the differences between groups for normal outcome variables simultaneously. Data analysis will be undertaken using SPSS (Statistical Package for the Social Sciences) with differences between treatment groups being considered statistically significant at *p *< 0.05. In addition, bivariate correlation and structural equation modelling techniques will be used to describe relationships among the various dependent and independent variables.

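### Age and height are said to drive change in BMI SD score but are neither stratification factors nor candidate covariates, so a little precision on BMI Z-score may be given up

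*Protocol article*

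**What the plan says.** Three sections of the protocol article bear on this.

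- **Sample size considerations.** The target is framed by the statement that "a 50% reduction in weight velocity over a 12-month period would be considered by the investigators as a successful outcome". BMI changes "of 0.26–0.58 SD can be expected among children over a one-year period", and the range is explained: "with the variation dependent upon age, degree of overweight, and height". The lowest value, 0.26, becomes the difference to detect.
- **Randomization.** "Stratification by gender and site is done". No other stratification factor is named.
- **Statistical analyses.** "Co-variates that may be used are: site, sex", followed by child and parent participation rates. The analysis is either a multi-level model, or a repeated measures ANOVA with an ANCOVA that adjusts the post-test for the pre-test.

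Age is known from screening (Table 1 admits children aged 5.5 to 9 years). Height is measured at the baseline anthropometry session.

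**The concern.** The article does not simply leave covariates to a later document: it names a set. That set omits two baseline characteristics that the article itself links to change in the outcome used to size the trial. If change in BMI SD score does depend on age and height, that dependence stays in the residual of the arm comparison, and a chance difference between arms in either factor is not adjusted for. What is at stake is the width of the confidence intervals for BMI Z-score.

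**Working it through.** **1. Where each factor appears**

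| Factor named in Sample size considerations | Stratified? | Candidate covariate? | Covered another way? |
|---|---|---|---|
| Degree of overweight | No | Not by name | Largely, through baseline BMI Z-score as the pre-test |
| Age | No | No | In part: a BMI Z-score is relative to age |
| Height | No | No | In part: height is a component of BMI |

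The mismatch is confined to age and height, and to whatever dependence of *change* on them remains after Z-scoring and baseline adjustment.

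**2. The plan's own figure**

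The article proposes "a sample size of 28 participants in each of the interventions, at each site". Its basis is an unadjusted two-group t-test at the 0.05 level, with 80% power for a BMI SD score difference of 0.26. No SD is given, so 28 cannot be reproduced forward. Solving backward (two-sided, 0.05, noncentral t):

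- 28 per group: the detectable standardised difference is 0.762, so SD = 0.26 / 0.762 = 0.341.
- 56 per group (two sites pooled, 2 × 28): the standardised difference is 0.534, so SD = 0.26 / 0.534 = 0.487.

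The analysed total is 28 × 3 arms × 2 sites = 168.

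**3. What adjustment could add**

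Let R² be the share of residual variance that age and height explain beyond the terms already in the model. The documents give no value, so 0.02 to 0.10 is assumed. Residual SD = SD × √(1 − R²), and the standard error falls by 1 − √(1 − R²). With SD 0.341 and 28 per group:

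| Extra R² | Residual SD | Fall in standard error | Power |
|---|---|---|---|
| 0 | 0.341 | – | 80% |
| 0.02 | 0.338 | 1.0% | 81% |
| 0.05 | 0.332 | 2.5% | 82% |
| 0.10 | 0.324 | 5.1% | 84% |

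With SD 0.487 and 56 per group the power column is the same to the nearest point, since both cases start at 80%.

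**4. A ceiling from the stated range**

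Suppose the whole 0.26 to 0.58 range were between-child spread that age and height predict.

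- Spread evenly: SD = 0.32 / √12 = 0.092. R² = (0.092 / 0.341)² = 0.073, power 83%.
- Every child at one end or the other: SD = 0.16. R² = (0.16 / 0.341)² = 0.22, power 89%.
- With SD 0.487 and 56 per group, R² is 0.036 and 0.108, power 81% and 84%.

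These are upper bounds, not estimates, for two reasons. The range is shared with degree of overweight, which the pre-test largely covers. It is also a one-year range, while the initial endpoint is 6 months. If half the spread had appeared by 6 months with the same outcome SD (an assumption), each R² is divided by four: 0.018 and 0.055 with SD 0.341, 0.009 and 0.027 with SD 0.487. The standard error then falls by roughly 0.5% to 3%.

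**The case against.** The strongest reply has four parts.

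**The range may describe the target effect, not error variance.** It follows directly from the 50% cut in weight velocity, and its lower end is used as the difference to detect. This reading is possible, and it is why the range cannot be turned into a firm R². It does not remove the point. All three arms are active and there is no untreated control, so if the same proportional cut yields different SD-score changes by age and height, that spread sits within every arm. Main-effect terms could absorb some of it.

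**A Z-score already allows for age, and BMI contains height.** This limits the size. But the article's range is itself in SD units and is still said to vary with age and height, so on its own statement some dependence remains.

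**Covariate choice belongs in an analysis plan.** The list is worded as optional, and a fuller plan may exist. That would answer a complaint about missing detail. Here the article names a list, and the list does not match its own account of what drives change.

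**Nothing planned is invalid.** This stands in full. A reader might infer that the omission biases the BMI Z-score comparison or leaves the trial below its stated power. The documents support neither inference. Allocation is random, so leaving out a baseline covariate causes no systematic error, and chance imbalance is already allowed for in the test's error rate. The sample size takes no credit for covariates, so omitting two cannot lower it. Nor does the article support the claim that a known, sizeable share of the variance is being left in the error: it gives no such share.

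**Conclusion.** The point holds as a modest matter of efficiency. The sample size and analysis sections do not fit together on age and height, and some precision on BMI Z-score may be lost as a result. The likely size is about 1 to 4 power points above the planned 80%. This rests on an assumed extra R² of 0.02 to 0.10, an SD back-solved from the stated sample size, and a two-sided test. The narrow age range, Z-scoring and baseline adjustment all argue for a small gain. The higher figures of 83% to 89% arise only if the entire one-year range is credited to age and height, and should not be quoted as an expected gain.

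**What to change.** In Statistical analyses, prespecify the BMI Z-score model to include, besides arm, baseline BMI Z-score, site, sex, baseline age and baseline height, and use the same set whether the multi-level model or the ANCOVA is run. For these terms, replace the optional wording with a firm commitment, so that age or height cannot be added or dropped once results are known.

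The cost is a sentence of analysis text and two degrees of freedom among about 168 analysed children. No new data, visits or participants are needed, and neither the randomization nor the sample size has to change. Whether participation rates belong in the model is a separate question that this change does not settle.
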